### Study procedure

The study will have three phases. During the first phase, subjects will be screened using the inclusion and exclusion criteria. Information on the implementation of the study and the objectives of the research will be given to each subject by trained staff and/or health care providers. Enrollment and tDCS treatment will be scheduled in the following weeks for eligible participants. The detailed procedure is displayed in Fig. 2.

**Fig. 2 Fig2:**
[figure not shown]
Randomized cross-over design for TIMBER (Standard Protocol Items: Recommendations for Interventional Trials (SPIRIT) figure)

The second phase will correspond to both inclusion of volunteers and the period of the tDCS sessions. All volunteers will have to sign the informed consent. Diagnosis will be established by an experienced psychiatrist, in accordance with DSM-5 criteria and confirmation by the SCID-II, as stated in the inclusion criteria section. Clinical assessment will be performed and behavioral baseline scores will be collected. Following completion of baseline clinical measures, subjects will be randomly assigned using a computer-generated randomization list with the information stored on a centralized computer to receive either active or sham tDCS. Predefined codes assigned to either real or sham stimulation will be used by trained staff and health care professionals to start the stimulator, allowing a double-blind study design. The first tDCS session will be delivered on a Monday. Two daily sessions will be performed during the following days up to Friday. The clinical and behavioral assessment will be performed once the last tDCS session has been delivered (day 5) and then 12 (day 12) and 30 days (day 30) following the start of the sessions.

Following the last assessment, subjects who underwent active stimulation sessions will then be submitted to sham sessions and vice versa (third phase). Then, once again, baseline measures will be performed before new sessions start, followed by evaluation immediately after their end and then 12 and 30 days after the start.

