Transcranial direct current stimulation (tDCS) is a promising, low-risk, non-invasive neuromodulation technique that relies on the application of a weak direct current of 1–2 mA to generate regional changes in cortical excitability, which, depending on the duration and the polarity, can last for several minutes up to a few hours after stimulation [10, 11]. Due to the key role of the prefrontal cortex in cognitive control, previous studies have applied tDCS over this cortical area in healthy subjects and clinical populations (with a diagnosis of depression, attention deficit/hyperactivity disorder, or substance abuse) and have reported a significant reduction of different aspects of impulsivity, such as inhibitory control, planning, delay-discounting, and risk-taking [3, 6–9]. tDCS over the prefrontal cortex may thus be a valuable therapeutic approach that can modulate impulsivity in BPD, leading to meaningful changes in suicidal and risky behaviors.

Hence, we propose to evaluate, for the first time, the clinical benefits of tDCS on reducing impulsivity in a BPD population. The main objective will be to investigate the efficacy of 1 week of bilateral tDCS (five consecutive twice-daily sessions), applied over the dlPFC of patients with BPD, in reducing impulsivity within the following 3 weeks. This study consists of a multicenter, sham-controlled, randomized crossover double-blinded trial, comparing active tDCS versus sham tDCS. We hypothesize that the active tDCS sessions would induce a greater reduction in impulsive behavior on risk-taking tasks compared to the sham sessions.

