### Outcomes

Task-based measures of behavioral and cognitive impulsivity will be administered before and after tDCS or sham stimulation. Additionally, EEG data will be collected during the BART, and resting-state EEG data will be collected pre- and post-tDCS administration to confirm engagement of the targeted brain region and to delineate the neural pathways underlying the effects of tDCS on impulsivity.

Our main efficacy criteria on reduction of impulsivity will be the amplitude variation of one specific evoked potential detected by EEG during the BART: feedback-related negativity (FRN). This reward-prediction error component is more negative when outcomes are worse than expected and more positive when they are better. The amplitude of the FRN will be compared before stimulation sessions and 5, 12, and 30 days after beginning active and/or sham tDCS.

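### Day 30 is both an efficacy visit and the crossover point, so a real effect lasting to day 30 would be overstated by the planned change-score comparison

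*Protocol article*

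**What the plan says.** All references are to the protocol article. Background describes a "sham-controlled, randomized crossover double-blinded trial, comparing active tDCS versus sham tDCS" and sets the main objective as efficacy of one week of stimulation "in reducing impulsivity within the following 3 weeks". Under Outcomes, the primary criterion is amplitude variation of the FRN: "The amplitude of the FRN will be compared before stimulation sessions and 5, 12, and 30 days after beginning active and/or sham tDCS". The secondary criteria use the same visits.

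Study procedure places the later visits at the end of the last session "and then 12 (day 12) and 30 days (day 30) following the start of the sessions". Patients then switch: "Following the last assessment, subjects who underwent active stimulation sessions will then be submitted to sham sessions and vice versa (third phase"). No interval and no return-to-baseline condition is given. A new baseline is planned: "Then, once again, baseline measures will be performed before new sessions start".

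Data management and statistical analyses compares active with sham by Student's t-test or the Wilcoxon test, and the EEG amplitude variation by Student's t-test or the Mann-Whitney test. Background also says that the excitability changes induced by stimulation "can last for several minutes up to a few hours after stimulation".

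**The concern.** A two-period crossover reads the second period cleanly only if the first period's effect has gone or stays constant through it. Here the visit at which a lasting effect would be seen is also the point after which patients switch. If the effect is there at day 30, the active-first patients carry it into their sham baseline. Their sham change then contains the fading of the active effect, which looks like worsening under sham and enlarges the active-minus-sham contrast.

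What is at stake is the size of a persistent effect, chiefly at day 30. That matters because the Discussion wants the results to inform the design of larger trials.

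**Working it through.** **The plan's own figure.** Sample size gives a difference of 2, SD 3, correlation 0.10, 5% significance, 90% power and 10% drop-out. Taking 3 as the SD of each change, the SD of the active-minus-sham difference is 3 × √(2 × 0.9) = 4.02. A two-sided paired t-test then needs 45 patients (power 0.903), and 45 / 0.9 = 50, as stated. (Taken literally as the SD of paired differences, 3 would give 26, or 29 with drop-out.) So the total of 50 relies on both periods being usable.

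**Bias formula.** Let τ_d be the true effect at day d, c0 the active effect still present at the second baseline, and c_d what remains of it at day d of period 2. Score improvement as positive, and assume that sham leaves no carry-over.
- Active-first: active change τ_d, sham change c_d − c0, difference τ_d + c0 − c_d.
- Sham-first: difference τ_d.
- Mean over two equal sequences (any common period effect cancels): τ_d + (c0 − c_d)/2.

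**Illustration under steady decay (assumed).** Take the planning difference of 2 as the day-5 effect and let half remain at day 30, so τ_30 = 1. Over the 25 days from day 5 to day 30 the effect halves, so t days after day 30 it is 0.5^(t/25). The gap before period 2 is not stated; 0 and 6 days are assumed.

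| Gap; time of second baseline | c0 | c_5 | c_30 | Day-5 estimate (true 2) | Day-30 estimate (true 1) |
|---|---|---|---|---|---|
| 0 days | 1.000 | 0.871 | 0.435 | 2.065 (+3%) | 1.282 (+28%) |
| 6 days; at new start | 0.847 | 0.737 | 0.369 | 2.055 (+3%) | 1.239 (+24%) |
| 6 days; at day 30 | 1.000 | 0.737 | 0.369 | 2.131 (+7%) | 1.316 (+32%) |

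Example, first row, day 30: 1 + (1.000 − 0.435)/2 = 1.282. Varying the share left at day 30 over its whole range, the day-5 estimate under these three settings never exceeds 2.13.

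**Limits.**
- Day-30 upper bound: c0 = τ_30 and c_30 = 0 give 1.5 × τ_30, or +50%.
- Carried effect constant through period 2: c0 = c_d, no bias.
- Nothing left at day 30: c0 = 0, no bias at any visit.

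**Precision of period 1 alone.** Two-sample t-test, two-sided 5%, SD of change 3 (assumed), no baseline adjustment:

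| Patients per arm | Power, difference 2 | Power, difference 1 | 95% CI half-width |
|---|---|---|---|
| 22 and 23 | 0.589 | 0.194 | 1.80 |
| 25 and 25 | 0.637 | 0.211 | 1.71 |

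The half-width is t × 3 × √(1/n1 + 1/n2); for 22 and 23 this is 2.017 × 3 × 0.298 = 1.80.

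**A carry-over pre-test.** With 45 completers and an SD of the two-period sum of 3 × √2.2 = 4.45, a between-sequence test has power of about 0.33 for a carry-over of 2 and 0.11 for 1.

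**The case against.** Several points on the other side stand.

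- About 25 stimulation-free days separate the last session from day 30. If the effect lasts minutes to hours, as Background says of excitability, this is ample washout. The objective's three weeks also end at about day 26, before the switch.
- An immediate switch is only a reading: the text gives no interval, and Fig. 2, to which it refers for the detailed procedure, is not shown. If the Monday start also applies to period 2, a few days could be added. The table shows that this changes the figures little.
- The baseline is re-measured. That removes a carried effect that stays constant, but not one that fades during period 2.
- The article condenses a full protocol, and a sensitivity analysis may stand there or in an analysis plan. The point therefore rests on the timing and the tests that the article does state, not on a claim that no other analysis exists.

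A reader might infer more than the documents support:

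- *That the trial cannot tell a lasting effect from contaminated baselines.* By the formula, contamination at the second baseline requires an effect that is still present. It can enlarge a real day-30 effect but cannot produce one.
- *That the bias could go either way.* For change scores, (c0 − c_d)/2 is never negative when the effect fades. An underestimate (τ_d − c_d/2) arises if raw follow-up values are compared, but the stated primary outcome is amplitude variation.
- *That the day-5 result is inflated by 25% or 50%.* This needs half or all of the effect to survive some 25 days and then vanish by day 5 of period 2. Steady decay gives 3% to 7%.

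**Conclusion.** The point holds in a limited form. With day 30 as both efficacy visit and crossover point, and change scores compared by the stated tests, an effect that persists to day 30 and then fades is overstated. The day-5 comparison is little affected under steady decay. The day-30 estimate is the vulnerable one: about +24% to +32% when half the effect remains, and at most +50%.

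These figures assume equal sequences, no carry-over from sham, steady decay (except for the 50% bound), an assumed gap of 0 or 6 days, and 2 as the day-5 effect; Sample size does not tie that difference to a visit. If the effect is short-lived there is no bias. The design need not be abandoned, but a day-30 crossover estimate should not be read alone.

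**What to change.** Keep the crossover comparison and pre-specify two additions, or confirm that the full protocol or analysis plan already has them.

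1. A period-1-only comparison of active with sham, adjusted for the pre-randomisation baseline, with 95% CI. It serves as a sensitivity analysis at day 5 and is reported beside any day-12 or day-30 persistence result. Period 1 is a randomised parallel comparison through day 30 and is free of carry-over.
2. The period-2-minus-period-1 baseline difference by sequence, with 95% CI. Under the assumptions above, the contrast between sequences estimates c0 directly. It should be descriptive only and should not decide which analysis is used, given how little power a carry-over test has here.

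The cost is analysis work on data already planned, with no extra visits or patients. The drawback is precision: with a CI half-width of about 1.7 to 1.8 before baseline adjustment, period 1 supports interpretation by estimate and interval and not by a significance test.

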### Sample size

Our primary efficacy outcome concerns changes in impulsivity by means of assessment of risk in conjunction with EEG measures. In this context, a sample size calculation based on an expected difference of 2 mV between the variation of amplitude of the FRN recorded by EEG during the BART, with a standard deviation for paired-differences of 3 and with an autocorrelation of 10% between measures in the same subject, was performed. Considering a significance level of 5%, a power of 90%, and a drop-out rate of 10% of patients, 50 patients should be included to meet the objectives of the study.

### Withdrawals

Subjects are informed before inclusion that they may withdraw their consent for treatment at any time during the study, with no need to justify their decision and without compromising their original follow-up or treatment in their respective service. Patients may as well be removed at any time from the study if one or more of the following is detected:Increase in suicide risk: observed in the third item of the HDRS and defined as an increase of 2 points for baseline scores between 0 and 2, and 1 point for a baseline score of 3Adverse eventsAny exclusion criteria

In all cases, patients will be conducted to specialized care and appropriate follow-up, granted by the national health insurance coverage. Every subject withdrawal will be registered, reporting motives as detailed as possible.

### Data management and statistical analyses

Collected information will be stored in physical files (Case Report Files (CRFs)), registered under each participant’s randomization code to respect confidentiality at all times. All researchers and trained staff called upon to collaborate in the tests are bound to secrecy. An anonymous electronic database (eCRFs) will be created, with controlled access, on the platform CleanWEB™, allowing multicenter data analysis.

All randomized patients will be used for the efficacy analyses. Qualitative variables will be described in terms of effective, absolute, and relative frequencies for each modality. Quantitative variables will be described in terms of minimum and maximum, quartiles, means, and standard deviations.

Comparison between active and sham stimulation will be based on the Student’s *t*-test for quantitative variables and the Wilcoxon test for semi-quantitative variables. The Student’s *t*-test or the Mann-Whitney test will be used for comparison of amplitude variation detected by the EEG. Analyses will be performed using Stata Software release 10.1 (StataCorp, Collège Station, TX, USA). No interim analyses will be performed.

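### The named tests cannot deliver the all-randomized efficacy analysis in this crossover, and the removal rule lets loss depend on the depression and suicidality outcomes

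*Protocol article*

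**What the plan says.** Four parts of the protocol article bear on this.

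- **Data management and statistical analyses.** "All randomized patients will be used for the efficacy analyses". The comparison of active with sham uses Student's t-test or the Wilcoxon test according to the type of variable. The EEG amplitude variation, which is the primary outcome, uses Student's t-test or Mann-Whitney. The section does not say whether the t-test is paired or which Wilcoxon test is meant, and it gives no rule for a patient with one period only.
- **Study procedure.** The second condition starts only after the day-30 assessment of the first: "subjects who underwent active stimulation sessions will then be submitted to sham sessions and vice versa (third phase").
- **Withdrawals.** "Patients may as well be removed at any time from the study if one or more of the following is detected". The triggers are a rise on the suicide item of the HDRS (item 3), adverse events, and any exclusion criterion. The exclusion criteria include use of antipsychotics or mood stabilizers.
- **Sample size.** The target is an FRN difference of 2 in the printed unit. The variability assumption reads "with a standard deviation for paired-differences of 3 and with an autocorrelation of 10% between measures in the same subject". The total is then raised to cover "a drop-out rate of 10% of patients".

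Under Outcomes, HDRS and C-SSRS are both secondary efficacy criteria, and the primary criterion is FRN amplitude.

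**The concern.** The analysis-set statement promises that everyone randomized counts. A patient removed during the first period has no data under the other condition, so a within-patient comparison cannot use that patient. As written, the tests and the removal rule lead to an analysis of patients with both periods, which could then be reported as all-randomized.

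The loss need not be random. One trigger is an item of a secondary efficacy scale, so patients who worsen on HDRS can leave because they worsened. C-SSRS measures a closely related construct. Starting a prohibited drug may also follow clinical deterioration. What is at stake is the interpretation of the depression and suicidality results and the truth of the all-randomized label. For FRN it is only a possibility.

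**Working it through.** **Step 1. Reproduce the 50.** Inputs from Sample size: difference 2 (in the printed unit), SD 3, correlation 0.10, significance level 5% (two-sided assumed, since the side is not stated), power 90%, drop-out 10%.

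- Take 3 as the SD of the change in each condition. SD of the paired difference = 3 × √(2 × (1 − 0.10)) = 3 × √1.8 = 4.02.
- Paired t-test, noncentral t: the smallest number of pairs with at least 90% power is 45 (power 90.3%). Then 45 / 0.9 = 50, the stated figure.
- Normal approximation: (4.02 × (1.960 + 1.282) / 2)² = 42.5, so 43 pairs, and 43 / 0.9 = 47.8, so 48.

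Other readings do not give 50:

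| Reading | Before drop-out | With 10% drop-out |
|---|---|---|
| 3 is the SD of the paired difference (literal) | 26 pairs | 29 |
| SD 4.02, one-sided 5% | 37 pairs | 42 |
| Correlation 0 | 50 pairs | 56 |
| Unpaired two-sample, SD 3 (normal approximation) | 48 per condition | 48 / 0.9 = 53.3, so 54 |

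The calculation that returns 50 is thus paired and counts the 5 drop-outs (50 − 45) as lost to the comparison.

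**Step 2. Follow a patient with period 1 only through each test.**

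- *Paired t or signed-rank:* no difference can be formed, so the patient is omitted and the all-randomized statement fails.
- *Unpaired t or Mann-Whitney:* the patient can be included if there is a post-baseline EEG, but the two periods of every completer are then treated as if they came from different people. At the plan's own correlation the variance of one difference is 2 × 9 = 18 instead of 2 × 9 × 0.9 = 16.2, a ratio of 1.11. The loss of precision is modest, but the analysis no longer matches the crossover or the basis of the sample size.
- *Either way:* a patient removed before any post-baseline EEG has no amplitude variation to analyse.

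**Step 3. Power.** With SD 4.02 and a difference of 2, power is 93.1% with 50 pairs, 90.3% with 45 and 86.5% with 40. If 3 is read literally as the SD of the paired difference, 40 pairs still give 98.4%. Power holds at the planned loss.

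**Step 4. Could removal shift the estimate?** This simulation is an illustration of an extreme case. It assumes SD 3, correlation 0.1, 10% removed, and removal decided entirely by the analysed outcome. Entries are the mean paired difference among completers.

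| Who is removed | True difference 2 | True difference 0 |
|---|---|---|
| Random 10% | 2.01 | 0.00 |
| Worst in period 1 | 1.78 | −0.01 |
| Worst in either period | 1.69 | 0.00 |
| Worst under sham only | 1.48 | −0.52 |
| Worst under active only | 2.53 | 0.51 |

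Removal that is symmetric between conditions leaves the null unbiased and shrinks a real effect. Removal tied to one condition moves the estimate by about 0.5 in either direction. These figures apply to FRN only so far as FRN is related to the triggers. If it is not, the shift is about zero.

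**The case against.** The other side has several good arguments.

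- *The text never says paired.* This is correct. Pairing is inferred from the design and the sample size. Mann-Whitney, named for the primary outcome, is unpaired and can take one-period patients. This changes the form of the difficulty but does not remove it, because the unpaired route discards the crossover structure (step 2).
- *Missing-data handling belongs in the analysis plan, which is not shown.* This stands against calling the absence of an imputation or available-data rule a fault. It is also ordinary to pair an all-randomized set with a sample size inflated for drop-out. It does not answer the conflict between what is stated: the analysis set, the tests and the removal rule. Nor can an analysis plan recover assessments that were not made.
- *Removal is discretionary, and the section says nothing about data collection afterwards.* Both are true. A reader might infer that every worsening patient is removed and never assessed again. The wording does not go that far. It permits removal from the study, and the follow-up it promises is clinical care. A rise found at a scheduled visit has also been recorded before the patient leaves.
- *Not every drop-out is lost or outcome-related.* Consent may be withdrawn for any reason, and someone leaving after day 5 of the second period has day-5 data under both conditions.
- *A mixed model does not by itself cure the selection.* This stands. An FRN model does not condition on HDRS item 3, adverse events or medication, and later period-1 visits do not supply the missing condition. Hence the sensitivity analysis below.

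A reader might also infer that the primary result is biased by a calculable fraction of the target, in favour of active. The documents give no relation between the triggers and FRN, and step 4 shows that the direction depends on which condition loses patients.

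**Conclusion.** The point holds in a limited form. The all-randomized commitment, the named tests and the permission to remove patients from the study cannot all be followed in this crossover. Paired tests lose patients without second-period data, up to 5 of 50 at the planned 10%. Unpaired tests ignore that each completer supplies both conditions.

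Loss can be directly related to HDRS, since one of its items is a removal trigger, and plausibly to C-SSRS. For FRN, bias needs a correlation with the triggers that the documents do not show. Its size and direction are undetermined, and it is about zero under the null if removal is symmetric between conditions.

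Power is adequate at the planned loss (90.3% with 45 pairs). That figure assumes a two-sided test, 3 as the per-condition SD and a correlation of 0.1, the only reading tried that returns exactly 50. The label attached to the SD of 3 is ambiguous, but that is a separate matter. The change is worth making while data are still being collected.

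**What to change.** 1. **Analysis.** Replace the simple tests with a likelihood-based mixed model with a patient random effect and terms for condition, period and visit, using every available period and visit. One-period patients then contribute. State plainly that a patient with no post-baseline value adds nothing to the contrast.
2. **Withdrawals.** Reconcile this section with the analysis-set statement by distinguishing stopping stimulation from leaving the study. Where the patient still consents, keep the assessments already scheduled and use them. The clinical removal triggers stay as they are.
3. **Reporting.** Tabulate removals by condition and reason (reasons are already to be recorded). Add a sensitivity analysis for removed patients, chiefly for HDRS and C-SSRS, for example assigning them an unfavourable value.

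The cost is a little more analysis work and some existing visits kept after stimulation stops. The sample size and visit schedule do not change.

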## Methods/design

### Study setting and overview

The research will be carried out in the psychiatric departments of three clinical centers in France (in the cities of Besançon, Nancy, and Rouffach), aiming to recruit 50 patients with BPD over the course of 2 years. Potential participants will be recruited from inpatient and outpatient services in each center. After they have been provided with a complete description of the study, written informed consent will be obtained. They will be assigned to two groups, and those who start by active stimulation sessions will then be submitted to sham sessions and vice versa (Fig. 1).

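### The Mann-Whitney option for the primary EEG outcome is an independent-samples test and does not fit the crossover or its paired sample-size calculation

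*Protocol article*

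**What the plan says.** All references are to the Protocol article.

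- **Design.** Under Study setting and overview, patients are split into two groups and "those who start by active stimulation sessions will then be submitted to sham sessions and vice versa". Study procedure adds that baseline is measured again before the second set of sessions, with the same follow-up schedule.
- **Primary outcome.** Under Outcomes: "Our main efficacy criteria on reduction of impulsivity will be the amplitude variation of one specific evoked potential detected by EEG during the BART". The component is the FRN.
- **Sample size.** The calculation assumes a difference of 2 (printed as mV) in FRN change and a within-patient correlation of 10%. Variability is given as a "standard deviation for paired-differences of 3". With 5% significance, 90% power and 10% drop-out it arrives at 50 patients.
- **Analysis.** Under Data management and statistical analyses, active and sham are compared by Student's t-test for quantitative variables and by a Wilcoxon test for semi-quantitative ones. A separate sentence covers the EEG outcome: Student's t-test "or the Mann-Whitney test will be used for comparison of amplitude variation detected by the EEG". Neither sentence mentions pairing, within-patient differences, sequence or period.

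**The concern.** Mann-Whitney compares two independent samples. Here the active and sham values come from the same patients, so with 45 completers the test would handle 90 correlated values as if they came from 90 people. The variance it uses leaves out the within-patient covariance that the sample-size section relies on. A Student's t-test has the same fault if it is run as a two-sample test on active against sham values.

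At stake is the agreement between the primary test and the power claim. The stated 90% belongs to a paired test, while one of the two named tests is unpaired. When measures within a patient are positively correlated, the unpaired standard error is too large, so the nominal 5% test rejects too rarely and power is lost.

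**Working it through.** **Inputs from the Sample size section:** difference 2 (unit printed as mV), SD 3, within-patient correlation ρ = 0.10, significance level 5%, power 90%, drop-out 10%. Sidedness is not stated; two-sided is assumed.

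**Step 1: reproduce the 50.** Take 3 as the SD of each condition's measure:

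SD of the paired difference = 3 × √(2 × (1 − 0.10)) = 3 × √1.8 = 4.025.

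A paired t-test (noncentral t) for a difference of 2 then needs n = 45, with power 90.3%. Allowing for drop-out, 45 / (1 − 0.10) = 50, which is the stated figure. The normal approximation gives 43, or 48 after drop-out.

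If 3 is read as labelled, as the SD of the paired differences, n = 26, and 26 / 0.9 = 28.9, so 29 patients. The label therefore does not reproduce 50. The per-measure reading does, and it is used below.

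**Step 2: the same inputs with an independent-samples t-test.** It needs 49 values per condition, or 55 after drop-out (49 / 0.9 = 54.4). At 45 per condition its nominal power is 87.9%.

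**Step 3: error in the standard error with 45 completers.**

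- Unpaired: 3 × √(2/45) = 0.632.
- Correct, paired: 4.025 / √45 = 0.600.
- Ratio: 1 / √(1 − 0.10) = 1.054, an overstatement of 5.4%.

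**Step 4: size and power by simulation.** There were 6,000 simulated trials per setting, with 45 completers (23 and 22 per sequence), SD 3 per condition, normal data and no period effect. Power is for a difference of 2. Only ρ = 0.1 comes from the protocol; 0.3 and 0.5 are assumptions.

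| ρ | SE ratio | Type I error %: paired t / unpaired t / Mann-Whitney | Power %: paired t / unpaired t / Mann-Whitney |
|---|---|---|---|
| 0.1 | 1.054 | 5.10 / 3.95 / 3.83 | 90.63 / 89.37 / 87.40 |
| 0.3 | 1.195 | 5.25 / 2.07 / 2.10 | 96.18 / 91.50 / 90.18 |
| 0.5 | 1.414 | 4.87 / 0.72 / 0.78 | 99.25 / 94.85 / 92.77 |

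At ρ = 0.1 a t-test on within-patient period differences between sequences, which adjusts for period, had 90.68% power, so the period term costs almost nothing. A separate run of that setting gave 87.6% for Mann-Whitney and 88.7% for the signed-rank test.

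**Step 5: sensitivity to the SD label.** If 3 is the SD of the differences, the per-condition SD is 3 / √1.8 = 2.24. With 45 completers at ρ = 0.1, power is then 99.1% (paired t), 99.0% (unpaired t) and 98.7% (Mann-Whitney). The SE ratio is still 1.054 because it depends only on ρ, but the power loss nearly vanishes.

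**The case against.** **The t-test may be meant as paired.** The text does not call it unpaired, and the sample-size section points to pairing. This stands: the definite mismatch is the Mann-Whitney option, and the t-test is only unqualified.

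**A two-sample test can be valid in a crossover.** A t-test or Mann-Whitney test on within-patient period differences, compared between the two sequences, is correct and removes period effects. The EEG sentence does not name the groups it compares. But nothing in the section mentions sequences or period differences, and the sentence before it compares active with sham. A reader following the text would not arrive at that analysis. The neighbouring Wilcoxon test does not settle the matter, since that name covers both the signed-rank and the rank-sum test.

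**The harm is small.** At ρ = 0.10 the like-for-like non-parametric loss is about 1 point of power (88.7% against 87.6%), and the type I error falls below 5%. This stands. A reader might infer that the crossover's advantage is thrown away or that false positives are inflated. The first would need correlations that the documents do not give, and the second runs opposite to the direction of the error.

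**Period effects.** A reader might also infer that leaving out a period term biases the result. The documents do not support that. The outcome is a change in amplitude and baseline is re-measured before the second period, so a stable shift in level between periods is subtracted. Only a difference in within-period change would remain. With balanced sequences even that costs precision and causes no bias. An assumed shift of 2 would lower power at ρ = 0.1 to about 84% (paired t) or 82% (Mann-Whitney), against about 90% with adjustment, but that shift equals the whole expected treatment effect.

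**Article format.** A condensed article may leave the period term and the rule for choosing between the two tests to the full protocol or SAP. Their absence is therefore not counted as an error here. Naming a test that conflicts with the design is a different matter.

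**Conclusion.** The point holds in a limited form. The Mann-Whitney test named for the primary EEG outcome, and Student's t-test if run unpaired, contradict the crossover design and the paired sample-size calculation. On the inputs that reproduce N = 50, an unpaired analysis overstates the standard error by about 5%, with a type I error of about 3.9% and power of about 89% (t) or 87–88% (Mann-Whitney) in place of 90%. The error is conservative.

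These figures assume 45 completers, a two-sided test, normal data and 3 as the SD of each measure. Larger losses depend on an assumed higher correlation. No bias from omitting the period term is shown with balanced sequences. Severity: should-fix.

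**What to change.** Replace the EEG sentence with one prespecified within-patient primary analysis of the change in FRN from each period's own baseline. Two suitable forms:

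- a mixed model with treatment, period and sequence effects and a random patient effect, reporting the active-minus-sham difference with its 95% confidence interval; or
- equivalently for patients with both periods, a t-test on within-patient period differences between the two sequences.

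As the non-parametric back-up, name a rank-sum test on those period differences between sequences, or the signed-rank test on active-minus-sham differences. Remove Mann-Whitney as a direct comparison of active and sham values. In the Sample size section, relabel the 3 as the SD of each measure if that is what was used.

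The cost is wording, plus about one degree of freedom for the period term, which is an inexpensive safeguard for precision. With 45 completers the planned 90% power is kept, and N = 50 does not change. The change should be made before unblinding.
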